# Learning to resist the urge: a double-blind, randomized controlled trial investigating alcohol-specific inhibition training in abstinent patients with alcohol use disorder

**DOI:** 10.1186/s13063-019-3505-2

**Published:** 2019-07-05

**Keywords:** Alcohol use disorder, Alcohol-specific inhibition training, EEG, Cortisol, Go-NoGo Task (GNG), Stop-Signal Task (SST), Implicit Association Test (IAT), Residential treatment, Drinking outcome

## Abstract

**Background:**

Alcohol use disorder (AUD) leads to a significant individual and societal burden. To achieve higher therapy success rates, therapeutic interventions still need to be improved. Most current neuroscientific conceptualizations of AUD focus on the imbalance between an enhanced automatic reaction to alcohol cues and impaired inhibition. Complementary to traditional relapse prevention strategies, novel computerized training interventions aim to directly alter these processes. This study tests a computerized alcohol-specific inhibition training in a large clinical sample and investigates its effects on behavioral, experimental and neurophysiological outcomes. It also analyzes whether variations in inhibition difficulty and/or endogenous cortisol levels during training impact these effects.

**Methods:**

This is a double-blind, randomized controlled trial (RCT) with 246 inpatients with AUD participating. After baseline assessment, participants are randomly assigned to one of three computerized Go-NoGo-based inhibition training interventions (two alcohol-specific versions with different Go/NoGo ratios, or neutral control training) and one of two intervention times (morning/afternoon), resulting in six study arms. All patients perform six training sessions within 2 weeks. Endogenous cortisol is measured in 80 patients before and after the first training session. Inhibitory control and implicit associations towards alcohol are assessed pre and post training, at which point electroencephalography (EEG) is additionally measured in 60 patients. Patients’ alcohol consumption and relevant psychological constructs (e.g., craving, self-efficacy, treatment motivation) are measured at discharge and at 3-, 6- and 12-month follow-ups. Fifty healthy participants are assessed (20 with EEG) at one time point as a healthy control group.

**Discussion:**

This study investigates the effects of a computerized, alcohol-specific inhibition training for the first time in patients with AUD. Results should give insight into the effectiveness of this potential add-on to standard AUD treatment, including proximal and distal measures and effects on behavioral, experimental and neurophysiological measures. Information about working mechanisms and potential optimizations of this training are gathered through variations regarding difficulty of inhibition training and training time. This study may thus contribute to a deepened understanding of AUD and the improvement of its evidence-based treatment.

**Trial registration:**

ClinicalTrials.gov, ID: NCT02968537. Registered on 18 November 2016.

**Electronic supplementary material:**

The online version of this article (10.1186/s13063-019-3505-2) contains supplementary material, which is available to authorized users.

## Background

Alcohol use disorder (AUD) is a major public health problem which has a substantial impact on patients’ psychological, physiological and social functioning [1–4]. Severe AUD often remains a lifelong condition due to patients’ susceptibility to relapse [5–7]. Despite the development of valuable treatment programs [8, 9], one third of patients relapse within 1 year after treatment, highlighting the need for effective new interventions to be added to these programs.

Current models of substance use disorders (SUDs) are based on neuroscientific research into subcortical alterations (e.g., [10–12]) and psychological investigations on implicit processes [13], and postulate on an imbalance between subcortical, implicit processes and cortical control processes. Briefly, these models assume that automated (subcortical) cue-reactivity is enhanced, thus leading to a strong drive to consume, while the opponent (cortical) executive control is weakened, making it difficult to inhibit this impulse (e.g., [11, 14–16]). The neuroscientific findings that underlie these models include enhanced reactivity to substance-related cues in brain regions related to reward prediction and saliency processing (e.g., nucleus accumbens, amygdala), habits and motivation (dorsal striatum, orbitofrontal cortex) and alterations in brain regions related to inhibitory control (dorsolateral prefrontal cortex, inferior frontal cortex and anterior cingulate cortex) [17, 18]. There is an extensive body of literature indicating that SUD is associated with impaired performance in inhibitory control tasks [19–24]. Until recently, these tasks did not differentiate between inhibition in a substance-related versus neutral context. However, this distinction seems to be clinically relevant, given that the central malfunction leading to relapse is the inability to exert inhibitory control in a substance-related context. Recent studies have suggested that alcohol-related inhibition demands additional neuronal resources in patients with AUD and heavy drinkers [25–28].

To translate the findings of impaired inhibitory control and enhanced cue-reactivity into a therapeutic context, an inhibition training for eating disorders [29–31] has been adapted into a novel alcohol-specific inhibition training and introduced into the field of AUD research [32, 33]. During this short, computerized, behavioral training, alcohol-related stimuli are consistently paired with a stopping response. Such an intervention might thus improve inhibitory control by training it on an explicit as well as a habitual level and possibly reduce cue-reactivity through stimulus devaluation.

The effect of one or two of these training sessions on alcohol consumption has been tested in regular drinkers [34, 35] and non-clinical, heavy drinkers [32, 33, 36, 37]. When alcohol consumption was assessed immediately after the training session, two studies found decreased consumption [35, 36], one study observed a non-significant trend in that direction [33], another study reported longer latency until participants took the first sip [37], and one study found no effects [34]. Of those studies assessing alcohol consumption 1 or 2 weeks post intervention, three studies reported decreased consumption after alcohol-specific inhibition training [32, 33, 37]. Note, however, that in two of these studies, the intervention was compared to a control condition, which could potentially have fostered alcohol consumption within the control group [32, 33]. Two other studies found no significant effects [34, 35]. In summary, while the effects of this training are inconsistent in non-clinical samples, it might be more effective in clinical populations where (1) the motivation to change drinking behavior is higher and (2) the impairment targeted by the training is assumed to be more pronounced at baseline. Therefore, it is important to test the feasibility and efficacy of the training in clinical populations with AUD. The present randomized controlled, double-blind study aims to close this gap, and includes follow-up measurements of drinking behavior and related concepts up to 12 months after treatment discharge, allowing assessment of potential clinically relevant long-term effects.

There are two putative working mechanisms by which alcohol-specific inhibition training is thought to be effective. The first is through enhancing inhibitory capacities in the context of alcohol-related cues, which can be assessed with inhibitory tasks, such as the Go-NoGo Task (GNG) or the Stop-Signal Task (SST). The second putative working mechanism regards devaluation of the stimuli. It is based on the *Behavior Stimulus Interaction Theory* [38], which states that the repeated stopping response to the rewarding (alcohol, in this context) stimuli causes a devaluation thereof [31, 33]. This mechanism is thus thought to alter the automatically attributed appeal of alcohol-related stimuli, an effect which can be measured with the Implicit Association Test (IAT).

With respect to the devaluation mechanism, the first two studies were consistent with predictions of the *Behavior Stimulus Interaction Theory* in their reports that participants’ implicit attitudes shifted towards a more negative evaluation of alcohol-related stimuli after alcohol-specific inhibition training [32, 33]. However, this finding could not be replicated in the four subsequent studies [34–37].

In regard to an inhibition-related working meachanism, those studies using the respective measures found no effects of GNG-based inhibition training on an SST [32, 37] nor flanker task [34]. However, these tasks measure slightly different inhibitory aspects (e.g., action cancellation in case of the SST) than the one affected during the GNG-based training (action restraint). The only study which assessed inhibitory functioning in the same form as targeted during training (i.e., measurement of inhibitory control with a GNG after a GNG-based training) reported no effects on reaction times during Go trials. Unfortunately, data on errors of commission (EOCs), which are a commonly used indicator of inhibitory capacities and an essential and proximal experimental outcome of a GNG-based inhibition training, were not reported in this study [36] and are thus still missing. Another important aspect concerns Go/NoGo ratio incorporated during training sessions. With one exception [34], most studies emloyed equiprobable GNG tasks with a Go/NoGo ratio of 50/50 during the training session. Such a ratio is unusually balanced for GNG tasks, where NoGo responses usually only make up 10–20% of the trials (e.g., [23, 24, 39]) in order to establish a high tendency to respond while making inihibition more demanding. Thus, it is possible that these versions failed to create the context of a prepotent Go response, in which inhibition could effectively be trained. The present study aims to extend prior research on potential working mechanisms by comparing two versions of this alcohol-specific inhibition training differing solely in the Go/NoGo ratio (thus in inhibition difficulty) and by comparing these versions’ effects on inhibitory capacities as well as on implicit associations.

With regard to other clinically important psychological variables, research has shown that outcome expectancies [40], self-efficacy to remain abstinent [41], motivation to change alcohol use [42] and craving [43] predict drinking outcomes at 1-year follow-up. These variables might thus act as potential mediators of effects in a clinical study. Furthermore, if the alcohol-specific inhibition training influences implicit associations towards alcohol, it might also affect explicit expectancies and/or subjective craving. The present study will, therefore, include these variables as potential outcomes and mediators in explorative analyses.

Taken together, the present study investigates the effects of an alcohol-specific inhibition training for the first time in a clinical sample using a randomized controlled, double-blind design with long follow-up periods. In doing so, the study contributes to research on potential working mechanisms by comparing two versions of the training which differ only in the Go/NoGo ratio and by the comparison of their effects on inhibitory functions and implicit associations. Explorative analyses will target psychological variables, such as craving, outcome expectancies, self-efficacy and motivation to change alcohol use. As the training’s rationale is anchored in neuroscientific research, we will also monitor neurophysiological effects with multi-channel electroencephalography (EEG) in order to investigate whether the training changes the neurophysiological correlates of alcohol-specific inhibition and/or implicit associations. Finally, prior research has shown that endogenous cortisol is a consolidation enhancer [44], which peaks in the morning [44, 45] and has been shown to improve effects of other learning-based therapies [46]. Since training procedures rely on learning processes affected by endogenous cortisol, we are, therefore, interested in whether its levels influence training effects.

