### Intervention

Participants in both versions of the Alc-inhibition training (Alc-IT) are, as the name suggests, trained in alcohol-specific inhibition: pictures of alcoholic beverages will be consistently paired with a NoGo cue, while Go cues will be distributed among the other picture types (water, neutral). In contrast, for patients in the control training group, all three picture types will be paired equally often with NoGo cues and Go cues (see Table 1).*Alc-IT (50/50)*: the first training group will operate with a Go/NoGo ratio of 50/50, as implemented in prior studies [32, 33]: This original version of the Alc-IT will include 80 alcoholic NoGo trials as well as 80 non-alcoholic Go trials. In order to match both Alc-IT versions in training length while keeping the number of Alc-NoGo pairings constant, an additional 80 neutral Go trials and 80 neutral NoGo trials were included*Alc-IT (75/25)*: the second version of the Alc-IT will operate with a Go/NoGo ratio of 75/25. It will equally include 80 alcoholic NoGo trials and 80 non-alcoholic Go trials, but contrary to Alc-IT (50/50) 160 neutral Go trials will complete the set. Both Alc-IT versions thus include the same number of Alc-NoGo pairings and are of the same length, but differ in their Go/NoGo ratio and thus in the difficulty regarding inhibition control*Control training*: the control group will receive a training that consists of 80 non-alcoholic, 80 alcoholic, and 160 neutral trials. This control training is thus a non-specific inhibition training which is of equal length to other two groups and includes the same number of alcohol-related pictures in it, but all pictures will appear with equal probabilities as Go or NoGo trials while the Go/NoGo ratio is kept at 50/50

**Table 1 Tab1:** Distribution of trial types in the three training versions

	Alc-IT (50/50)		Alc-IT (75/25)		Control training	
	Trial type		Trial type		Trial type	
Picture types	Go	NoGo	Go	NoGo	Go	NoGo
Alcohol	–	80	–	80	40	40
Water	80	–	80	–	40	40
Neutral	80	80	160	–	80	80
Total trials	320		320		320	

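### The two Alc-IT versions differ in more than the Go/NoGo ratio, so a difference between them cannot be attributed to inhibition difficulty alone

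*Protocol article*

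**What the plan says.** The Background of the protocol article states twice that one feature separates the two alcohol-specific trainings: they are "differing solely in the Go/NoGo ratio (thus in inhibition difficulty"), and the study contributes by "comparing two versions of the training which differ only in the Go/NoGo ratio". The first statement equates the ratio with difficulty. The Intervention section lists what is matched (alcohol-NoGo pairings and length) and again infers a difference in difficulty from the ratio. The Abstract names inhibition difficulty as a factor whose effect will be analysed, and as a source of information on working mechanisms.

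The Intervention section and Table 1 give the composition per session:

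- Alc-IT (50/50) "will include 80 alcoholic NoGo trials as well as 80 non-alcoholic Go trials"; to equalise length, "an additional 80 neutral Go trials and 80 neutral NoGo trials were included".
- Alc-IT (75/25): "It will equally include 80 alcoholic NoGo trials and 80 non-alcoholic Go trials". The other half of the session is filled differently from the first version: "160 neutral Go trials will complete the set".
- Control training: each picture type is split evenly between Go and NoGo, "while the Go/NoGo ratio is kept at 50/50".

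The limitation in the Discussion concerns only the possibility that the control training improves general inhibition. It does not mention the composition of the two alcohol-specific versions.

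**The concern.** If two versions differ in one feature only, a difference in outcome can be assigned to that feature. If a second feature moves with it, the randomised comparison still estimates the effect of one version against the other, but not which feature caused it.

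Here the second feature is how well the picture predicts the required response. Picture and letter cue appear together (Intervention), so picture type is available as a signal. A rarer NoGo is the article's reason to expect harder inhibition. A picture type that fully predicts the response could work the other way, or could act through stimulus devaluation, the second mechanism described in the Background. A 75/25 versus 50/50 difference on the Go-NoGo Task, the Stop-Signal Task, the IAT or drinking would then have more than one explanation, although the text promises one.

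**Working it through.** **Inputs.** Table 1 cell counts per session (Go / NoGo) and six sessions, both from the Intervention section.

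| Picture type | Alc-IT (50/50) | Alc-IT (75/25) | Control |
|---|---|---|---|
| Alcohol | 0 / 80 | 0 / 80 | 40 / 40 |
| Water | 80 / 0 | 80 / 0 | 40 / 40 |
| Neutral | 80 / 80 | 160 / 0 | 80 / 80 |

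**Step 1: reproduce the stated ratios.**
- 50/50: Go 80 + 80 = 160, NoGo 80 + 80 = 160, total 320, so 50%/50%.
- 75/25: Go 80 + 160 = 240, NoGo 80, total 320, so 75%/25%.
- Control: Go 40 + 40 + 80 = 160, NoGo 160, total 320, so 50%/50%.

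The stated ratios and lengths are correct.

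**Step 2: what else differs between the two Alc-IT versions.** The alcohol and water rows are the same, so everything comes from the neutral row.

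| Quantity | 50/50 | 75/25 |
|---|---|---|
| P(NoGo given neutral picture) | 80/160 = 0.50 | 0/160 = 0 |
| P(NoGo given non-alcohol picture) | 80/240 = 0.33 | 0/240 = 0 |
| Alcohol share of NoGo trials | 80/160 = 50% | 80/80 = 100% |
| P(NoGo given alcohol) minus P(NoGo given non-alcohol) | 1 − 0.33 = 0.67 | 1 − 0 = 1.00 |
| Best accuracy from picture type alone | (80 + 80 + 80)/320 = 75% | (80 + 80 + 160)/320 = 100% |
| NoGo trials over six sessions | 6 × 160 = 960 | 6 × 80 = 480 |
| Neutral NoGo trials over six sessions | 6 × 80 = 480 | 0 |

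Best accuracy from picture type alone is the sum, over picture types, of the larger of the Go and NoGo counts, divided by 320. In 75/25 the letter cue is redundant throughout; in 50/50 it is needed on the 160 neutral trials, half the session.

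**Step 3: where the difference arises.** Before neutral trials are added, each version has 80 alcohol NoGo and 80 water Go trials, and picture type fixes the response on all 160. The neutral trials create both the ratio difference and the contingency difference. With 320 trials and 80 alcohol-NoGo pairings fixed, a 25% NoGo share is 0.25 × 320 = 80 trials, so every NoGo trial must be alcohol.

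**Step 4: comparisons with control.** 50/50 and control match on ratio and on stops per session (160 each). They differ in the alcohol row (0/80 versus 40/40) and also in the water row (80/0 versus 40/40). 75/25 versus control differs in pairing, in ratio and in stops (80 versus 160).

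**The case against.** The strongest defence is that the extra differences are largely the ratio seen from other sides. At fixed length, 50% versus 25% NoGo is 160 versus 80 stops; with pairings also fixed, the alcohol share of NoGo trials follows. This stands: number of stops, alcohol share and ratio should not be counted as three independent confounders. It explains why the contingency changed, but does not make *solely* or *only* true, because the neutral pictures still behave differently.

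A reader might infer that only 75/25 lets patients use the rule that alcohol means stop. Table 1 does not support that: alcohol is always NoGo in both versions, and the difference lies wholly in the neutral pictures.

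A reader might also infer that predictability cancels the intended difficulty. That is possible but not shown. Participants are told to respond to the letter cue, and nothing in the article indicates how far they would rely on the picture. The article's reason for expecting 75/25 to be harder remains plausible.

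The consequence is also limited. The numbered research questions compare Alc-IT with control, the Study aim describes the ratio as an additional investigation, and Table 1 discloses the full composition. Against this, learning about mechanisms by varying difficulty is a declared aim in the Abstract and the Background, so the wording affects what the trial may conclude.

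**Conclusion.** The concern holds in a limited form. The Background claims a design property that Table 1 shows the trial does not have. The versions differ in ratio and also in picture-to-response contingency: P(NoGo given neutral) 0.50 versus 0, alcohol share of NoGo trials 50% versus 100%, best accuracy from picture type alone 75% versus 100%. A 75/25 versus 50/50 difference therefore cannot be attributed to inhibition difficulty alone.

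Three stronger conclusions are not supported. Difficulty is not excluded as an explanation; it is one of several. The randomised comparisons of the versions as packages are not invalid, and no power or sample-size figure changes. Alc-IT (50/50) versus control is not a clean test of alcohol specificity: it is matched on ratio and stops but combines alcohol-NoGo with water-Go pairing. The absence of named contrasts or interval estimates from the article is no defect either, since these can stand in an analysis plan that is not shown.

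The counts come directly from Table 1 and need no assumption. How strongly the contingency affects behaviour is unknown.

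**What to change.** 1. In the Background, strike *solely* and *only*. State that 75/25 versus 50/50 tests the ratio together with a more exclusive alcohol-NoGo contingency and the absence of neutral stopping, and that this follows from holding pairings and length constant.
2. In the Intervention section, stop treating the ratio difference as equivalent to a difficulty difference. Limit the mechanism conclusion to match, and add the point to the limitations in the Discussion.
3. State that only 50/50 versus control is matched on ratio and number of stops, that even this contrast mixes alcohol-NoGo with water-Go pairing, and that 75/25 versus control mixes pairing with ratio.
4. If trial-level training data are kept (the article does not say), report commission errors on the 80 alcohol-NoGo trials per session common to both versions. This would describe whether 75/25 was harder on balance, without separating ratio from predictability. The overall error rates noted after each session cannot serve: they mix omission and commission errors over different numbers of NoGo trials (160 versus 80).

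The training programs, randomisation and data collection stay as they are. Under Trial status, data collection was still running, and the Statistics section places the main analyses after it, so the wording could be settled before results are known. The cost is a narrower mechanism claim.

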#### Other

Additionally, two other measures will be used: experienced emotions as well as the capability of the participant to experience and regulate these emotions will be measured with the *Emo-Check* [86, 87]. The *Trail Making Test A and B* (TMT A & B [88]) screens for neuropsychological executive function by assessing visual attention and task switching. Previous research with preclinical samples indicates that executive functions could influence the relationship between alcohol-related implicit cognitions and addictive behaviors ([89, 90], but see [54]). Consequently, the TMT will be used as a covariate in the statistical analyses.

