#### T1: Inclusion and baseline assessment

During the second treatment week, a member of the study team will conduct an interview to confirm the AUD diagnosis (DIA-X adapted to DSM-5 criteria; [55]). To assess the drinking quantity of the 90 days prior to detoxification, the TLFB interview will be conducted [59, 60]. Furthermore, a psychological assessment with a test battery consisting of questionnaires will also take place at this time point.

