#### Main study

Training effects on our primary outcome measures (PDA and HDD at 3-month follow-up) will be assessed with a 2 × 3 analysis of variance (ANOVA) with the factors time point (T1, T5) and training group (Alc-IT (50/50), Alc-IT (75/25) or control). Further, a Cox regression will be computed to predict the effect of the intervention on TFD (at 3-month follow-up).

Training effects on experimental test parameters will be assessed with a 2 × 2 × 3 repeated measures ANOVA with the factors measurement point (T2, T3), time of day (morning, afternoon) and training group (Alc-IT (50/50), Alc-IT (75/25) or control). Where Mauchly’s test of sphericity indicates heterogeneity of covariance, we will verify repeated measures results with Greenhouse-Geisser corrections.

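### The stated primary models use no pre-training self-efficacy, motivation, craving or expectancy score; pre-specifying them would be a low-cost efficiency gain, not the repair of an error

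*Protocol article*

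**What the plan says.** All references are to the protocol article.

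- **Prognosis.** Background names outcome expectancies and then says "self-efficacy to remain abstinent [41], motivation to change alcohol use [42] and craving [43] predict drinking outcomes at 1-year follow-up". It gives them this role: "The present study will, therefore, include these variables as potential outcomes and mediators in explorative analyses".
- **Measurement before training.** At T1, "a psychological assessment with a test battery consisting of questionnaires will also take place at this time point". The T2 section places a further series of questionnaires, with stress and craving ratings, before the first session. The discharge section says that the questionnaires of previous time points are used again. Which scale is given at which visit is in a figure that is not shown.
- **Primary models.** Under Statistics, Main study, PDA and HDD "will be assessed with a 2 × 3 analysis of variance (ANOVA) with the factors time point (T1, T5) and training group". For TFD, "a Cox regression will be computed to predict the effect of the intervention on TFD (at 3-month follow-up").
- **Covariates.** The only one named is the Trail Making Test, under Interviews and questionnaires, Other: "Consequently, the TMT will be used as a covariate in the statistical analyses". The reason given is its possible influence on the link between implicit cognition and addictive behavior.
- **Sample size.** Power calculation requires 244 patients for PDA/HDD (f = 0.2, α = 0.05, power 0.8) and 174 for TFD, and plans to recruit 246.

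**The concern.** The protocol calls four constructs predictive of drinking and collects questionnaires before training, yet the stated primary models use none of the four. The one covariate it names is justified on other grounds. Variation in drinking that pre-training scores could explain therefore stays in the error term for PDA and HDD. In the Cox model, leaving out prognostic variables moves the estimated hazard ratio somewhat towards 1 and costs power. TFD has most room to gain: the PDA/HDD model at least contains the T1 value of the outcome, while the stated TFD model contains no prognostic information.

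The mediator role does not stand in the way. Mediation concerns values after training; adjustment would use values from before it.

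**Working it through.** **1. Reproduce the plan's figure.** Inputs from Power calculation: f = 0.2, α = 0.05, power 0.80. Noncentral F test with 2 numerator degrees of freedom and λ = f²N. At N = 244, λ = 0.04 × 244 = 9.76 and power is 0.800, so the stated 244 is reproduced. At N = 246, λ = 9.84 and power is 0.804. The plan reaches its target without covariates.

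**2. PDA/HDD with covariates.** Let R² be the share of the residual variance of the T5–T1 change that the pre-training scores explain. The protocol gives no value, so a range is shown. Then λ = f²N/(1 − R²), the standard error is multiplied by √(1 − R²), and four error degrees of freedom are removed.

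| Assumed R² | λ at N = 246 | SE factor | Power at N = 246 | N for 80% power |
|---|---|---|---|---|
| 0 | 9.84 | 1.00 | 0.804 | 244 |
| 0.02 | 10.04 | 0.99 | 0.812 | 240 |
| 0.05 | 10.36 | 0.975 | 0.825 | 232 |
| 0.10 | 10.93 | 0.949 | 0.846 | 220 |
| 0.20 | 12.30 | 0.894 | 0.887 | 196 |

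If the scores explain nothing, the four degrees of freedom cost less than 0.1 percentage point of power. With 10% loss (0.9 × 246 ≈ 221), power is 0.757 without covariates and 0.802 at R² = 0.10.

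**3. How the covariates must enter.** With two time points, the group-by-time test is the same as a one-way comparison of the T5–T1 difference between groups. A covariate with the same coefficient at T1 and T5 cancels out of that difference and leaves the test unchanged. The figures in step 2 apply only if the covariate enters with a time interaction, or in an ANCOVA of T5 or of the change.

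**4. TFD.** Simulated Cox models with 246 patients, censoring at day 90 and one prognostic score with log hazard ratio 0.3 to 0.7 per SD. All of these inputs are assumptions.

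- 50% of controls drinking by day 90, true hazard ratio 0.6: the gain is about 2 points at log hazard ratio 0.3 and about 8 at 0.7. Separate runs of this last setting gave up to 11. The unadjusted hazard ratio moves to about 0.61–0.64.
- 30% of controls drinking, hazard ratio 0.5: about 1 to 7 points.
- 30% of controls drinking, hazard ratio 0.6: at most about 4 points.
- 20% of controls drinking, hazard ratio 0.6: at most about 3 points.

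A fair summary is 1 to 8 points. The upper end needs both a high event rate and a strong predictor.

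**5. Reserve.** PDA/HDD: 246 − 244 = 2 patients. TFD: 246 − 174 = 72 patients.

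**The case against.** The strongest reply is that nothing here is wrong. An unadjusted randomized comparison is valid, and the stated 244 reproduces. A journal article may also leave the covariate list to the full protocol or analysis plan. The Main study section is evidently not a complete list of model terms, since the Trail Making Test covariate is missing from it. This stands, and it is why the point is a recommendation and not a defect.

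Three further replies also stand and limit the size.

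- Background speaks of prediction at 1 year, while the primary outcomes are at 3 months. No correlation or R² is given. For PDA/HDD only what the scores add beyond T1 drinking counts.
- The only relapse rate in the article is one third within 1 year. First drink and relapse can differ, but this gives no support for assuming that 50% of controls drink by day 90.
- The references behind the predictive statement (40 to 43) are mostly not those cited for the scales. AASE-G is 65, SOCRATES 62, OCDS-G 61 and CAEQ 66 and 67. Only the single confidence item about abstinence in one year shares a reference (41) with the self-efficacy statement.

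A reader might infer that the plan throws away a known amount of precision, or that all three primary outcomes are sized with almost no reserve. The documents support neither. The loss cannot be sized from them, and the thin margin is confined to PDA/HDD. Nor is the shift of the unadjusted hazard ratio a bias in the trial: the unadjusted and adjusted hazard ratios are different quantities.

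The mediator role is no answer to the point, and the wording of the primary models does not exclude covariates.

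**Conclusion.** The point holds as an inexpensive efficiency improvement. The protocol calls these constructs predictive, gives questionnaires before training, and does not list the constructs in its primary models. The planned analysis remains valid and powered as stated.

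For PDA and HDD the gain at n = 246 is about 1 percentage point of power at 2% explained variance, 2 at 5%, 4 at 10% and 8 at 20%. For TFD it is about 1 to 8 points. These figures rest on assumed prognostic strength, on assumed event rates and effects for TFD, and on prediction at 1 year carrying over to 3 months. They also assume that all four constructs are measured before training. The T2 section states this for a craving rating; for the other scales it is inferred from the discharge section.

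**What to change.** Before the main analysis, pre-specify a small set of pre-training scores, one per construct:

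- self-efficacy: for example the single confidence item, which shares its reference with the Background statement, or AASE-G;
- craving: one named measure;
- motivation: one named measure;
- outcome expectancies: one named score, or a stated reason for leaving them out.

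Enter these scores as covariates in the Cox model for TFD. For PDA and HDD, enter them as covariate-by-time terms in the time-by-group model, or use an ANCOVA of T5 or of the T5–T1 change. Say explicitly that only pre-training values are used and that T3 and T4 values are kept for the mediation analyses.

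The cost is wording, a few degrees of freedom and a simple rule for filling in a missing questionnaire. The TFD hazard ratio becomes conditional on the covariates and should be reported as such. No new data are needed. When the article appeared, data collection was still running and the main analyses were to follow its completion, so pre-specification was still possible.
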